#### Quantitative Data Collection and Analysis

The baseline survey will take place in year two of the project in 60 communities in the 6 wards of the Toro Local Government Area. In each community, a team of interviewers will cover a cluster of 100 households, recording questionnaire responses on android handsets using ODK software (Get ODK) [78]. They will upload records to a Cloud server via the cellular network, and we will download data sets for analysis. The analysis will use CIETmap open-source software (version 2.2.21; CIET group) [79], which interfaces with the R programming language (R Core Team). The household survey of adolescents and parents will provide data on the frequency of the specified ASRH outcomes and individual and family factors potentially related to these. Institutional reviews of health facilities serving the communities will provide data about potential supply-side determinants. Key informant interviews with community leaders and opinion-makers and community profiles will record factors at the community level potentially relevant to ASRH outcomes.

The follow-up survey will cover the same 60 communities as the baseline survey, but not necessarily the same households.

##### Data Collection Instruments

ASRH questionnaires for adolescents and adults will draw on existing validated instruments [80-82], contextualized by findings of the focus groups and FCM. They will include intermediate outcomes of knowledge, attitudes, and experience amenable to change stimulated by the intervention in a short time scale.A guide for institutional reviews of health facilities will gather information on available ASRH services in one clinic per communityA questionnaire for key informants and a community profile proforma will enquire about factors relevant to ASRH at the community level. Key informants will include traditional and religious leaders, headteachers, health facility heads, and social workers.

##### Quantitative Data Analysis

Bivariate and then multivariate analysis of responses to the baseline survey will examine associations between ASRH outcomes and potential determinants at individual, family, and community/services level, using the Mantel-Haenszel procedure [83], with the Lamothe cluster adjustment [84]. The analysis will include gender as a key variable in the examination of ASRH outcomes and associations with these outcomes.

To measure the impact of the intervention, we will compare the pre-specified ASRH outcomes at follow-up between adolescents in SEPA and non-SEPA wards and compare the change from baseline to follow-up between SEPA and non-SEPA wards. We will use generalized estimating equations to account for clustering (at ward and community levels), differences at baseline, known potential confounders, and any other community-level changes in the period [85]. A supplementary analysis will look at changes in outcomes in relation to the SEPA implementation ‘score’ (see Process Evaluation of the SEPA Intervention) in individual SEPA communities.

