**Methods:**

The participatory research project is a sequential mixed-methods codesign of a pragmatic cluster randomized controlled trial. Focus groups of local stakeholders (female and male adolescents, parents, traditional and religious leaders, service providers, and planners) will identify local priority ASRH concerns. The same stakeholder groups will map their knowledge of factors causing these concerns using the fuzzy cognitive mapping (FCM) technique. Findings from the maps and a scoping review will inform the contextualization of survey instruments to collect information about ASRH from female and male adolescents and parents in households and from local service providers. The survey will take place in 60 Bauchi communities. Adolescents will cocreate materials to share the findings from the maps and survey. In 30 communities, randomly allocated, the project will engage adolescents and other stakeholders in households, communities, and services to discuss the evidence and to design and implement culturally acceptable actions to improve ASRH. A follow-up survey in communities with and without the intervention will measure the short-term impact of these discussions and actions. We will also evaluate the intervention process and use narrative techniques to assess its impact qualitatively.

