#### Sample Size

The sample for the baseline and follow-up household survey will include 6000 adolescent girls and 4000 adolescent boys, plus 4000 mothers and 2500 fathers. The clinical trials simulator of Taylor and Bosch [75] estimates study power for the indicative outcome of the experience of violence by adolescent girls. With an expected prevalence of about 20% at baseline, and a sample of 3000 girls in 30 SEPA communities and 3000 in 30 non-SEPA communities, a 15% reduction of gender violence (to 17%) would be detectable with 80% power at the 5% level (κ=0.05). We anticipate a household response rate of around 95%. In a previous Bauchi household survey, the response rate was 96% (3.4% were not available, and 0.4% declined) [76].

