#### Allocation of the Intervention

We will stratify the wards by size and proportion of urban communities, and an epidemiologist not involved in the fieldwork will randomly allocate (using a computer-generated random sequence) 3 of the 6 wards to receive the SEPA intervention. All the 30 study communities in the 3 SEPA wards will participate in SEPA. We do not expect any community to decline to participate; they all participated in and strongly valued our recent home visits program [40,77].

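### Six wards are randomised, but the named analysis is GEE: without both a small-sample-corrected variance and a t reference on at most 4 df, a nominal 5% test has about 18.5% type I error

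*Protocol article*

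**What the plan says.** Under Allocation of the Intervention, an epidemiologist outside the fieldwork will "randomly allocate (using a computer-generated random sequence) 3 of the 6 wards to receive the SEPA intervention". Every study community in a chosen ward receives it, so the ward is the unit randomised. The allocation is restricted: "We will stratify the wards by size and proportion of urban communities". The survey covers "60 communities in the 6 wards of the Toro Local Government Area" (Quantitative Data Collection and Analysis), which is 10 communities per ward on average.

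Quantitative Data Analysis compares outcomes at follow-up between the arms and will also "compare the change from baseline to follow-up between SEPA and non-SEPA wards". The method is named: "We will use generalized estimating equations to account for clustering (at ward and community levels", together with baseline differences, confounders and community-level changes. No variance estimator, small-sample correction, reference distribution or degrees of freedom is given.

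Two other places bear on the point. Sample Size claims 80% power for 20% versus 17% from 30 versus 30 communities and does not mention wards. The abstract gives a different unit: "In 30 communities, randomly allocated, the project will engage adolescents and other stakeholders".

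**The concern.** The usual GEE robust variance is justified when the number of independent clusters is large. Here the randomised comparison is 3 versus 3. The uncorrected variance is then biased downward, and the Wald statistic is far from normal.

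Ordinary GEE also takes one clustering level. With the ward as that level there are six clusters. With the community as that level there are 60, but communities in one ward were allocated together, and any real difference between wards is left out of the standard error.

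The project sets out to test effectiveness and to inform policy. If the ordinary form of the method were used, a significant result would be weak evidence and the interval would overstate precision.

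**Working it through.** **Inputs from the article.** 6 wards, 3 per arm; 60 communities; 3000 girls per arm (100 per community); 20% versus 17%; 5% level, taken as two-sided; κ = 0.05. **Assumptions.** Equal ward sizes, 10 communities per ward, and every between-ward SD or coefficient of variation (CV) below. The article gives no between-ward figure.

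**1. The plan's own power figure.** Read κ as the CV between communities and treat the 60 communities as independent:

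Var = [0.20×0.80 + 0.17×0.83]/3000 + 0.05²×(0.20² + 0.17²)/30 = 0.00010037 + 0.00000574 = 0.00010611

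SE = 0.0103 and 0.03/0.0103 = 2.91. Power is 83% with a normal reference and 82% with t on 58 df, close to the stated 80%. Reading κ as an intracluster correlation gives 23%. The stated power therefore reproduces with communities, not wards, as the independent units.

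**2. GEE clustered on wards.** With a treatment term only and equal wards, each arm contributes Σ(ward mean − arm mean)²/9 to the uncorrected robust variance. The unbiased version divides by 2×3 = 6. The ratio is 6/9 = 2/3, so the SE is √(2/3) = 0.816 of what it should be, about 18% too small. The properly scaled statistic is t on 4 df, so rejecting at 1.96 means rejecting when |t₄| > 1.96×0.816 = 1.60.

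| Variance | Reference | Two-sided type I error |
|---|---|---|
| Uncorrected robust | normal | 18.5% |
| Uncorrected robust | t, 4 df | 8.6% |
| Unbiased (Kauermann-Carroll in this layout) | normal | 12.2% |
| Unbiased (Kauermann-Carroll in this layout) | t, 4 df | 5.0% |
| Mancl-DeRouen | t, 4 df | 2.7% |

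Interval width relative to the width needed: 0.816×1.96/2.776 = 0.58.

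The 18.5% does not depend on the intracluster correlation. Simulating the logistic version (40,000 trials per setting, ward and community correlations each between 0 and 0.05) gave 17.9% to 18.4%. Fitted exchangeable linear-link GEEs (2,000 trials each, both correlations set at 0.01; some fits reached the iteration limit) gave 17.1% unadjusted, 18.5% for change from baseline and 19.8% adjusted for baseline.

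**3. GEE clustered on communities only.** Take a community SD of 1 point (0.05×20%), binomial variance 0.16/100 = 0.0016, and ward SD s.

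True variance = 2[s²/3 + (0.0001 + 0.0016)/30]

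Expected estimate = 2[(0.0001 + 0.0016) + s²×20/29]/30

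- s = 0: the two agree, so 5.0% (5.9% once the slight small-sample bias with 60 clusters is counted)
- s = 1 point: 0.000180 against 0.000118, SE ratio 0.81, error 11.3%
- s = 2 points: 0.000380 against 0.000132, SE ratio 0.59, error 24.9%

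**4. Randomisation test.** Unrestricted allocation has 20 arrangements (6 choose 3), so the smallest two-sided p is 2/20 = 0.10. Stratification leaves fewer arrangements. With three pairs there are 2³ = 8, and the floor is 2/8 = 0.25.

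**5. Power of a valid ward-level test.** Add (ward CV)²×(0.20² + 0.17²)/3 to the variance in step 1 and use noncentral t on 4 df, critical value 2.776.

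| Assumed ward CV | SE | 0.03/SE | Power |
|---|---|---|---|
| 0 | 0.0103 | 2.91 | 60% |
| 0.05 | 0.0128 | 2.35 | 43% |
| 0.10 | 0.0183 | 1.64 | 24% |

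Dropping the community term changes these only to 62%, 44% and 25%.

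**The case against.** The strongest reply is that the article does not specify the failing test. It names GEE and the clustering levels and leaves the variance and reference open. Such detail is often left to an analysis plan, and none is shown. GEE clustered on wards with a Kauermann-Carroll or Mancl-DeRouen variance and t on 4 df fits the text and holds the error at 5.0% or 2.7%.

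This stands, and it limits the claim. A reader might infer that the planned test will produce a false positive about one time in five; the article does not support that as an unconditional statement. Nor does it support calling the standard errors far too small. They are about 18% too small at ward level, and a large part of the inflation comes from the normal reference.

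It is also fair that the article mentions wards as a clustering level, so ignoring them is not what it says, and that the community-level error rates rest on assumed ward SDs. A ward SD of 2 points is a CV of 0.10, twice the only between-cluster figure in the article.

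What remains is more than an omitted detail. The article fixes a many-cluster method for six randomised units, and its power calculation shows no sign that inference rests on six. The method in its ordinary form is invalid here, and correcting only the variance or only the reference does not make it valid.

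Finally, the abstract can be read as randomising communities. If that were so, the problem would largely disappear. But the allocation section sets out the actual procedure ("3 of the 6 wards to receive the SEPA intervention"), and the analysis section compares wards, so the ward reading is the better supported one.

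**Conclusion.** The concern holds in conditional form. With 3 versus 3 wards, GEE clustered on ward has a two-sided type I error of about 18.5% at nominal 5% unless a small-sample-corrected variance and a t reference on at most 4 df are both used. That figure assumes equal wards, a treatment-only model, an uncorrected robust variance and a normal reference; it needs no assumed intracluster correlation. Clustering on communities alone inflates the error by an amount set by between-ward variation, which the article does not give.

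Two things do not follow: that the article commits to the uncorrected test, or that GEE cannot be used at all. A separate consequence does follow. A valid analysis on six wards does not have the stated 80% power, even with no variation between wards (60%).

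**What to change.** 1. State that inference on the intervention effect is at ward level, by one of two routes: compare covariate-adjusted ward summaries 3 versus 3 with a t-test and interval on at most 4 df; or fit GEE with the ward as cluster, a named small-sample-corrected robust variance and the same t reference. Use fewer df if strata are conditioned on.
2. If a randomisation p-value is reported, give its floor: 0.10 for unrestricted 3-of-6 allocation, and higher under the stratification actually used (0.25 if wards are paired).
3. Restate power with the ward as the unit, over a stated range of between-ward variation.
4. Reconcile the abstract's account of communities being randomised with the ward allocation in the methods.

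The analysis change costs some wording and a few lines of R. Its consequence is larger: intervals become wider, roughly 1/0.58 = 1.7 times those of the uncorrected ward-level GEE, and the 80% power claim is lost. No analysis wording restores that power, because the limit is the number of wards randomised. Allocating communities individually would largely remove the problem, but that is a change of design.

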#### Qualitative Evaluation of Impact

Drawing on the most significant change technique [86], we will collect stories of life changes that participants attribute to the SEPA intervention. These stories can reveal both expected and unexpected effects of the intervention. This narrative approach complements quantitative evaluations, shedding light on possible mechanisms of effect. Sampling is usually purposive and should aim to include a range of experiences and views [87,88].

In intervention communities, local researchers will identify a purposive sample of 60 storytellers, including at least 25 adolescent girls and 15 adolescent boys. The sample will include people likely to have had a range of different experiences depending on their age, gender, urban or rural residence, role in the community, and extent of involvement in SEPA. Fieldworkers will collect stories by taking notes as the storytellers speak, reading back the stories to them to check for accuracy.

A hybrid thematic analysis [53,54] of the narratives will include a deductive analysis using the CASCADA results chain as a framework, supplemented by an inductive analysis of other themes emerging in the narratives.

#### Auditing Trial Conduct

A project steering committee led by the Bauchi State Primary Health Care Development Agency and including relevant government bodies and the research team will meet twice-yearly for oversight and decision-making.

### Ethical Considerations

#### Ethical Approval

On 1 March 2021, the Bauchi State Health Research Ethics Committee approved the overall project (NREC/03/11/19B/2021/03). On 13 September 2021, the Faculty of Medicine and Health Sciences Institutional Review Board at McGill University (A09-B51-21B) approved the initial qualitative phase of focus groups and FCM and will be asked to approve the baseline and follow-up survey and implementation of the intervention of evidence-based dialogues.

#### Consent

Local research supervisors will seek consent from community leaders to work in each community. Facilitators will seek oral informed consent from group participants and parental/guardian consent for participants under 18 years old. Facilitators will ask participants to respect each other’s confidentiality and stress that they should not share personal information in the group setting. For the household survey, interviewers will seek and record on the handset oral informed consent from all respondents. They will also seek parental consent for adolescents under 18 years old.

#### Confidentiality and Data Access

Parents or guardians will not be present during adolescent group activities or individual interviews. We will not record any names or identifying information alongside responses from individuals. Group reports will not identify individuals. Fieldworkers will conduct group sessions in a private location. They will not proceed with household interviews unless they can establish and maintain privacy. Data on the server are password protected; only designated research team members will have access.

#### Minimizing Potential Harms

Survey respondents, especially females, who disclose sensitive issues, like domestic violence, might face retribution if other household members hear of this. Ensuring privacy minimizes this risk. Discussing topics like experiencing violence or abuse might cause distress. Interviewers will carry details of local support services. Facilitators will refer any group participant who is disturbed by the discussion to pre-arranged support in the community.

Fieldworkers, particularly women, potentially face security threats. All fieldworkers will be from the local area. Each fieldwork team will include male members, part of whose role is to ensure the safety of their female colleagues. Government focal points in each ward will advise on any current security risks, and the teams will not visit insecure communities.

### Dissemination and Capacity Building

The Bauchi State Primary Health Care Development Agency will convene meetings at state and zonal levels to discuss findings and policy implications with planners and decision-makers in government, NGOs, and development partners. In year three, the project will share findings from the FCM and baseline survey, and in year five, discuss the impact of the SEPA intervention.

Evidence about factors related to ASRH outcomes in Nigeria and how these might be improved will fill a gap in the literature. We will also publish articles about participatory methods and advances in their analysis, of interest beyond the field of ASRH research. We plan to publish at least five open access papers in peer-reviewed journals and present findings in two international conferences.

#### Capacity Building

The mainly female research team will consolidate their skills in participatory methods and learn about recent advances. The senior team members will support junior members and knowledge users to analyze and present findings and write articles for publication. Officers from the State Ministry of Health and Primary Health Care Development Agency will work on the project and learn about participatory, qualitative methods and collecting reliable survey data. In year five, the research team will facilitate an analysis and interpretation workshop over 18 days for 20 women and men from the government and FOMWAN. Participants will practice analysis techniques using project data. The research team will support them in preparing articles for publication. Adolescents will design materials to share the evidence from FCM and the baseline survey, including video docudramas. We will help them to create videos and other materials, and they will build skills as they do so.

## Results

Focus groups exploring ASRH concerns of stakeholders began in October 2021. Baseline data collection in the household survey is expected to take place in mid-2022.

## Discussion

The project will demonstrate the feasibility of implementing ASRH interventions in a Muslim and conservative culture. It tests a participatory approach: adolescents and other stakeholders share their knowledge, codesign instruments to collect data about ASRH and share the findings, participate in evidence-informed dialogue, and codesign and implement culturally appropriate solutions.

Methodological innovations will have wider relevance. We will test FCM with adolescents and continue our advances in the analysis of these maps. We will refine our use of transitive closure to analyze shifts in intermediate outcomes after an intervention [89].

During the project, adolescents and other stakeholders will identify interventions at different levels, from individual to policy level, to improve ASRH in Bauchi, that can be implemented by adolescents, by communities, and by services. Some will be implemented and have a measurable impact during the project; others are long-term interventions, and measurement of their impact is beyond the scope of this project. The interventions will be specific to the culture of Bauchi, but the way we develop them with stakeholders could have much wider resonance. The project could pave the way for a full-scale randomized controlled trial of the participatory intervention across different contexts.

By training and working with planners and decision-makers, the project will support the adoption of evidence-based policies to improve ASRH in Bauchi. It will contribute to a culture of evidence-based planning of health services, building on previous work in the State by the research team.

Evidence about factors related to ASRH outcomes in Nigeria and implementation and testing of a dialogic intervention to improve these outcomes will fill a gap in the literature. The project will document and test the effectiveness of a participatory approach to ASRH intervention research.

## Appendix

Multimedia Appendix 1 Peer review report from the CIHR/ISRC (Canada) Project Grant Committee.

## Abbreviations

ASRH: adolescent sexual and reproductive health
CASCADA: conscious knowledge, attitude, subjective norms, intention to change, agency to change, discussion of issues, and action to change
FCM: fuzzy cognitive mapping
FOMWAN: Federation of Muslim Women’s Associations in Nigeria
NGO: nongovernment organization
SEPA: socializing evidence for participatory action
